### Adherence Measures

Intervention adherence will include the percentage of IDWL lessons viewed and frequency of self-monitoring energy intake, weight, and aerobic exercise minutes entered into the study website (or transmitted to the study website via the Fitbit app) by participants over the study duration. Attendance at live yoga and wellness classes will also be assessed. Additional adherence metrics in the yoga condition include the number of times each prerecorded yoga video was viewed and weekly minutes per week of yoga practice (reported on the study website). During months 13‐18, self-reported yoga practice will be assessed via monthly surveys.

### Trial Monitoring, Safety, and Adverse Events

Upon study enrollment, participants will be instructed to contact the study staff should they experience any illnesses, injury, or side effects that are distressing to them throughout the 18-month research study. Moreover, each month, randomized participants will be required to complete a brief survey, which asks about any injuries or illnesses over the past month. Should a participant report an injury or illness on this survey, they will be contacted by the research staff to gather more information. Finally, at each assessment period (3, 6, 12, and 18 months), participants will be asked to report any illnesses, injuries, changes in health status, and medications experienced since the previous assessment. All adverse events (AEs; any untoward medical occurrence in a person that is temporarily associated with participation in the clinical study) will be reported by the principal investigator (JU) to the institutional review board, the trial’s data safety monitoring board, and funding sponsor. Serious AEs (any AE that results in 1 or more of the following: death, life-threatening event, inpatient hospitalization, persistent or significant disability or incapacity, and important medical event based on appropriate medical judgment) will be reported within 24 hours. All other AEs will be reported twice yearly and will be included within regular reporting to the data safety monitoring board (consisting of external reviewers who have been approved by the study sponsor).

### Data Analytic Plan and Sample Size Considerations

#### Sample Size Considerations

This study is fully powered for the primary aim, which is to examine treatment effects on WL from baseline through follow-up, taking into account the initial 3-month WL period. Power was calculated using a combination of G*Power and MPlus Monte Carlo estimation. Effect sizes were based on a preliminary study assessing the effects of yoga for WL that showed within the yoga condition, there was significant WL from 3 to 6 months (Cohen *d*=0.45). Effect sizes from both yoga and contact-matched control arms were used to estimate a between-group effect at follow-up to use in the power calculations (difference in median percent WL of 3.5% between conditions among those with high initial WL; 95% CI 0.005-0.139). Assuming a similar effect size, 20% correlation between covariates, a total sample size as low as 146 would yield sufficient power (>80%) for testing between-group effects on WL from baseline. However, the final sample size was inflated to 210 to account for (1) the possibility that the effect size estimates that were obtained from our pilot work and used to determine the sample size were not generalizable, (2) adequately powered secondary aims (secondary outcomes and mediation), and (3) attrition rates similar to what we have seen in past studies by this research team (<20% of randomized sample at the end of treatment).

#### Analysis and Statistical Methods

Prior to analyses, data will be cleaned and explored, including outlier analysis and censoring of implausible values. Sociodemographics (eg, age, biological sex, and race or ethnicity), baseline weight, height, and BMI will be summarized across the aggregate sample and compared between groups using 2-tailed *t* tests for continuous variables, chi-square analyses for categorical variables, and nonparametric tests as appropriate. The distribution of each of the primary and secondary study outcomes will be assessed using both parametric and graphical methods and transformed as necessary (eg, log transform toward normality). Potential distributions for the outcome variables include normal and zero-inflated distributions. *P* values will be adjusted for multiple comparisons using the Hommel method. All analyses will be on the intent-to-treat sample (everyone randomized at 3 months will be included in the final analysis). Sensitivity analyses will explore effects of those who provide information during the postenrollment or prerandomization period that might influence outcomes (eg, initiation of WL medication).

#### Primary Aim

We will examine treatment effects on weight change from baseline to 18 months using a longitudinal mixed effects regression model. Absolute weight will be regressed on treatment assigned (YOGA vs WELLNESS), initial WL (from baseline to 3 months), and identified confounders. Model estimates and group comparisons will be generated for the 12-month primary end point, with contrasts specified to allow for understanding group differences in the postrandomization period (eg, 3‐12 months controlling for baseline to 3 months). Models will include a participant-specific intercept and random slope terms to adjust for repeated measurements within participants over time. Further, we will test for clustering by cohort and adjust, if needed. Mixed models are flexible, in that they allow for a wide range of specifications of the time effect (linear and nonlinear), which is particularly important in WL data, where outcomes do not necessarily follow a linear pattern over time.

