Yoga and wellness classes will be delivered via videoconferencing software (ie, Health Insurance Portability and Accountability Act [HIPAA]–compliant Zoom; Zoom Video Communications). There will be no intervention during months 13‐18. Randomization will occur at the 3-month assessment (ie, 3 months into the IDWL) in equal numbers based on a permuted block randomization procedure with small, random sized blocks, stratified by biological sex, racial or ethnic minority status, and percent WL achieved during the first 3 months of the WL program (<5% vs ≥5% WL). The randomization scheme was generated by the study statistician using R Studio (version 3.6.0) and uploaded into REDCap directly (to ensure study staff was kept blinded toward the full schematic). Participants will be recruited in cohorts over the study period. Assessments of weight, aerobic PA minutes, dietary lapses, potential lapse triggers (eg, affect, craving, and dietary temptations), and self-regulation mediator variables will be measured at baseline, 3 months (just prior to randomization), 6 months (mid-treatment), 12 months (postintervention), and 18 months (following a 6-month period of no intervention). At each assessment period, data will be collected via a series of REDCap questionnaires, an Actigraph accelerometer, and a 10-day EMA protocol (ie, 5 surveys per day over 10 days with each survey taking 2‐5 minutes to complete).

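### Two of the three stratification factors, sex and minority status, are not named as covariates in the primary model, and its confounder term leaves the adjustment set open

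*Protocol article*

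**What the plan says.** Study Overview (Protocol article) allocates participants 1:1 in permuted blocks of small, varying size. The allocation is "stratified by biological sex, racial or ethnic minority status, and percent WL achieved during the first 3 months of the WL program", with the weight-loss factor cut at 5%. Three two-level factors give 2 × 2 × 2 = 8 strata.

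Primary Aim models absolute weight. Besides treatment, the covariates it gives are "initial WL (from baseline to 3 months), and identified confounders". It adds that "Models will include a participant-specific intercept and random slope terms to adjust for repeated measurements within participants over time", and for recruitment cohort that "we will test for clustering by cohort and adjust, if needed". Sex and minority status do not appear among the named terms. Secondary Aims adjusts for the baseline value of the outcome and again for confounders that are not listed.

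Sex and race or ethnicity are named in Exploratory Aims, but only as possible moderators of the effect on weight. Analysis and Statistical Methods says that sociodemographics, "baseline weight, height, and BMI will be summarized across the aggregate sample and compared between groups", using t tests, chi-square tests or nonparametric tests.

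**The concern.** Stratified blocks force near-balance between arms on the stratification factors. Where those factors predict the outcome, the treatment estimate varies less than under simple randomisation. A model that omits them leaves their variation in the residual, so its standard error is larger than the estimate's true variability. The usual remedy is to put the stratification factors in the model. Here one of the three is covered and two are unnamed.

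The second part is the open term. In a randomised comparison, baseline differences between arms arise by chance, so there is no confounding to discover in the usual sense. Covariates are chosen because they are prognostic, and they can be named beforehand. An unlisted set lets the covariates of the single primary comparison be settled once data are visible. At stake are a little power and the prespecification of the primary test, not protection against false positives from the missing strata.

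**Working it through.** **The plan's own figures.** The article gives no figure for the variance explained by the strata. Sample Size Considerations gives 146 in total as the smallest adequate sample. If its d = 0.45, a within-yoga-arm change, is treated as a between-arm difference, a two-sided 5% test with 80% power needs 156 in total. With the variance multiplied by 1 − 0.2² = 0.96, it needs 150. The between-arm effect in SD units is not stated, so 146 can be neither properly reproduced nor called wrong, and it says nothing about the strata.

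**Inputs from the article.** 210 randomised 1:1; 8 strata; attrition taken as 20% (stated as below 20%), leaving 168; 35% men and 40% from minority groups (the minimum enrolment targets in the Discussion).

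**Assumptions.** Two-sided 5% test; block sizes 2 and 4; about half of participants at or above 5% loss; random dropout; d = 0.45 for illustration only; one 12-month outcome analysed by linear regression in place of the mixed model. R² is the share of residual variance, given initial weight loss, explained by sex and minority status together.

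**Simulation, 6,000 runs per setting.** The first three result columns use initial weight loss as the only covariate; the last column adds sex and minority status. The SE ratio is mean model SE divided by empirical SE, under no effect.

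| R² (assumed) | SE ratio | Type I error | Power | Power with both added |
|---|---|---|---|---|
| 0% | 1.006 | 5.0% | 82% | 82% |
| 5% | 1.014 | 4.9% | 83% | 84% |
| 10% | 1.036 | 4.1% | 84% | 87% |
| 25% | 1.113 | 3.1% | 85% | 91% |

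With both factors added, the ratio is about 1.00 and type I error is 5.0% to 5.4%. Simulation error is about √(0.05 × 0.95 / 6000) = 0.3 percentage points on type I error and about 1/√(2 × 6000) = 0.9% on the ratio. The 5% row is therefore barely distinguishable from no effect.

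**Where the loss arises (R² = 10%).** Without the two factors, the model SE is 0.1544 and the empirical SE 0.1490. With them, these are 0.1467 and 0.1470. The true variability hardly changes, because the blocks already deliver most of the gain; what changes is the reported SE.

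**Analytic check (R² = 10%, 168 analysed, SD 1, exact balance).**
- Reported SE without the factors: 2/√168 = 0.1543. True SE: 0.1543 × √0.90 = 0.1464.
- Power without: Φ((0.45 − 1.96 × 0.1543)/0.1464) = Φ(1.008) = 84%.
- Power with: Φ(0.45/0.1464 − 1.96) = Φ(1.114) = 87%.
- The adjusted analysis reaches the lower power with 4 × 0.90 × (1.96 + 1.008)²/0.45² ≈ 157 participants. Omission therefore costs 168/157 ≈ 1.07, about 7% of the sample.

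**Main effects or all eight strata.** At R² = 10%, adding all eight stratum indicators to initial weight loss gives 86% power, against 87% for the two main effects. The finer form gains nothing.

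**The case against.** The strongest reply is that sex and minority status are unnamed, not excluded: they may be among the confounders intended, and a condensed article may leave the list to an analysis plan not shown here. That stands in part. The article does not say they will be left out, so the standard-error error is conditional. But it does set out the primary model's covariates, and the term it uses commits to no list.

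Several stronger readings are tempting and are not supported:

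- *The model ignores the strata altogether.* Initial weight loss is the variable underlying the third factor, so two of three are unnamed, not all three.
- *Baseline significance tests will choose the covariates.* A reader might infer this because no other between-arm baseline procedure is described. The article does not link those tests to the model, and the confounders may have been identified in advance. A 40% chance of a spurious flag (1 − 0.95¹⁰) would need ten independent tests. The section names six variables: BMI is computed from weight and height, and two are tied to stratification factors. The other four would give 1 − 0.95⁴ = 18.5% if independent, and that matters only if the link is assumed.
- *Omission wastes 1/(1 − R²) of the sample, or 11% at R² = 10%.* That overstates it: the calculation above gives about 7%, since stratification has already reduced the true variance.
- *Cohort must be a compulsory fixed effect, or the 5% category added on top of initial weight loss.* Allocation was not stratified by cohort, and the category adds almost nothing beside the continuous variable. Neither follows from the design argument.

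**Conclusion.** The point holds in limited form. Two design factors collected on every participant are not named in the primary model, and the adjustment set is open-ended as written. If the two factors are omitted and are prognostic, the model SE is about 1% to 4% too large for R² of 5% to 10%, and power falls by about one to three percentage points at an illustrative d = 0.45. The error is conservative: it gives no extra false positives.

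The size rests on an assumed R² and on a single-time-point approximation. It also depends on how baseline weight enters. If baseline is part of the outcome vector or a covariate, so that the contrast is within-person change, the share explained by sex should be small. If absolute weight were analysed without it, the share could approach the 25% row, where the SE is about 11% too large. Primary Aim does not name baseline weight as a covariate, so the article alone does not settle this. It does not support a claim that the standard errors are certainly wrong or that covariates will be picked by significance tests.

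**What to change.** In Primary Aim and Secondary Aims, state that the models include sex and minority status as prespecified fixed effects alongside 3-month weight loss. Replace the open confounder term with a closed list fixed before outcome data are examined, and state that it is not chosen from between-arm baseline tests. The baseline comparisons can remain as description.

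The cost is wording and about two degrees of freedom. No new data are needed. The article reports enrolment still open, with four of five cohorts launched, so the change can be made before analysis.

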#### Secondary Aims

Using a similar analytic approach as that described for the primary aim, we will examine intervention effects on secondary outcomes, including frequency of dietary lapses and potential lapse triggers (eg, affect, cravings, and ability to resist dietary temptations), as assessed via EMA. Namely, longitudinal mixed effects models will be specified that regress outcomes over time on intervention group (YOGA vs WELLNESS), time, intervention*time, baseline value of the outcome, and confounders. Models will also adjust for the clustering of data within participants. Effects of day and measurement period will be tested, and adjustments made, as needed.

To evaluate the secondary aims of this study, we will examine potential mediators (eg, affect, mindfulness, self-compassion, and distress tolerance) of the treatment effect on primary (ie, weight change) and secondary outcomes (ie, dietary lapses) using a multiple mediator model with bootstrapped SEs (10,000 bootstrapped samples). Models estimate the path coefficients (a path: effects of YOGA vs WELLNESS on changes from baseline in potential mediators and b path: effects of changes from baseline in potential mediators on WL or lapse outcomes) as well as the indirect effect of intervention (ab path: YOGA vs WELLNESS on outcomes through the mediators).

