### Outcome Measures

#### Overview

Assessments of weight, aerobic exercise minutes, dietary lapses, potential lapse triggers, and self-regulation mediator variables will be measured at baseline, 3 months (just prior to randomization), 6 months (mid-treatment), 12 months (postintervention), and 18 months (following a 6-month period of no intervention). Both questionnaires and EMA will be used. Research staff members will not be blinded to group assignment, and efforts will be made to collect data from all enrolled participants at the time of each assessment, including those who may no longer be attending intervention classes. Brief descriptions of study measures are provided below.

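### Secondary-outcome models adjust for the month-0 value and omit the 3-month value taken just before randomisation, which gives away precision

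*Protocol article*

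**What the plan says.** The secondary analysis is introduced as "Using a similar analytic approach as that described for the primary aim", and its terms are then listed: "longitudinal mixed effects models will be specified that regress outcomes over time on intervention group (YOGA vs WELLNESS), time, intervention*time", with the list ending in "baseline value of the outcome, and confounders" (Secondary Aims).

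The Overview under Outcome Measures says that weight, exercise, lapses, triggers and mediators "will be measured at baseline, 3 months (just prior to randomization), 6 months (mid-treatment), 12 months (postintervention". The Study Overview states that "Randomization will occur at the 3-month assessment". Baseline and the 3-month visit are therefore separate assessments, and only the second immediately precedes allocation.

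For weight, the Primary Aim section adjusts for "initial WL (from baseline to 3 months), and identified confounders" and asks for contrasts covering the period after randomisation. Study Aims places the secondary comparison of lapses and triggers at 12 months.

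**The concern.** The article uses baseline consistently for month 0, so the stated covariate was taken before three months of weight loss treatment that both arms share. A measurement of the same outcome just before allocation is collected but does not appear in the term list. The weight model accounts for the first three months; the secondary list does not.

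There are two consequences. First, if the 3-month value predicts the 12-month value beyond what month 0 already explains, leaving it out makes the standard errors larger than they need be. Sample Size Considerations relies on 210 participants partly to give adequate power for the secondary aims, so this matters. Second, the section does not name the outcome visits. The role of the 3-month visit (covariate, outcome row, or neither) is left open, and some ways of settling it would distort the effect estimate.

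**Working it through.** **The plan's own figure.** The article gives a minimum of 146, raised to 210, for the primary weight outcome, and no separate power figure for secondary outcomes. The 146 cannot be properly reproduced, because alpha, the between-group standardised effect and the SD are not stated. The within-arm d = 0.45 in a two-sided 5% comparison at 80% power would give 156. Nothing below depends on these figures.

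**Inputs.** From the document: 210 participants, equal allocation, attrition below 20%. Taking the full 20%, 210 × 0.8 = 168, or 84 per arm. Assumed, because the document gives none: the correlations of one outcome between months 0, 3 and 12, written r03, r0 and r3 (r0 and r3 being the correlations of months 0 and 3 with month 12), and a true effect of 0.40 SD.

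**Residual variance of the 12-month outcome (total variance 1).**
- Month 0 only: 1 − r0²
- Month 3 only: 1 − r3²
- Both: 1 − (r0² + r3² − 2·r0·r3·r03) / (1 − r03²)

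Example, r03/r0/r3 = .6/.4/.6:
- Month 0 only: 1 − 0.16 = 0.840
- Month 3 only: 1 − 0.36 = 0.640
- Both: 1 − (0.16 + 0.36 − 0.288)/0.64 = 0.6375

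Required sample size is proportional to residual variance, so the ratios below are ratios of N.

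| r03/r0/r3 | Month 0 | Month 3 | Both | Month 0 ÷ month 3 | Month 0 ÷ both |
|---|---|---|---|---|---|
| .5/.5/.5 | 0.750 | 0.750 | 0.667 | 1.00 | 1.12 |
| .5/.4/.5 | 0.840 | 0.750 | 0.720 | 1.12 | 1.17 |
| .6/.4/.6 | 0.840 | 0.640 | 0.6375 | 1.31 | 1.32 |
| .7/.5/.7 | 0.750 | 0.510 | 0.510 | 1.47 | 1.47 |

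**Power** with 84 per arm and an assumed effect of 0.40 SD:

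| r03/r0/r3 | Month 0 | Month 3 | Both |
|---|---|---|---|
| .5/.5/.5 | 84.9% | 84.9% | 88.8% |
| .6/.4/.6 | 80.7% | 90.0% | 90.1% |
| .7/.5/.7 | 84.9% | 95.3% | 95.3% |

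**If month 3 were an outcome row.**
- Categorical time, arm difference free at every visit: the 12-month contrast is unbiased, but the month-3 data add nothing to it. Under .6/.4/.6 its residual variance stays at 0.840. Setting the month-3 arm difference to zero lowers it to 0.6375, the same as adjusting for both values.
- Arm effect averaged over 3, 6, 12 and 18 months: a constant effect of 1 from month 6 becomes (0 + 1 + 1 + 1)/4 = 0.75.
- Linear time trend in the arm difference, ordinary least squares: mean time = 9.75, slope = 6.75/132.75 = 0.0508, so the fitted effect at month 12 is 0.75 + 2.25 × 0.0508 = 0.86 instead of 1.

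**The case against.** The best defence is that the secondary models are said to follow the primary approach, which does separate the periods before and after randomisation. That may be the intention. But the listed terms say specifically what the secondary models contain, and they include neither a month 0–3 term nor a post-randomisation contrast. The opening phrase does not clearly fill the gap.

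A second objection is that an article may leave the list of outcome visits to the analysis plan. That is fair, and the absence of the list is not itself an error. The covariate, however, is stated.

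Three stronger readings are tempting, and the documents do not support them:
- **Month 3 is analysed as follow-up and dilutes the effect by 25%.** The text never says that month 3 is an outcome row. The model contains an arm-by-time term and the comparison is set at 12 months, so a visit-averaged effect is not the planned estimate. A linear trend is not specified either; the Primary Aim section allows linear or nonlinear time.
- **Chance imbalance at month 3 biases the result.** Allocation happens at that visit, so the 3-month values are balanced in expectation. Any residual imbalance is sampling variation already reflected in the standard error. It is the same precision loss and should not be counted twice.
- **The loss is large and known.** With a favourable pair such as r0 = 0.6 and r3 = 0.8, the ratio for replacing month 0 by month 3 is 0.64/0.36 = 1.78. No correlation is documented, and with equal correlations that ratio is 1.00.

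The formulas also assume a normal outcome. Lapses are counts, and Analysis and Statistical Methods allows for zero inflation, so the ratios carry over only roughly.

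**Conclusion.** The point holds as one of efficiency and clarity for the secondary outcomes. The stated covariate is the month-0 value, although a later pre-randomisation value of each outcome is collected. The 12-month contrast with categorical time is not biased, and the primary weight model is not affected.

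Under the assumed correlations, month-0 adjustment alone needs about 1.12 to 1.47 times the N of adjusting for both values. The lower end is the equal-correlation case at .5; the upper end has correlations that decay with time. In large samples, adding the 3-month value never raises residual variance above that for month 0 alone. Distortion of the effect is conditional: it needs month 3 as a follow-up row together with an averaged effect or a linear trend, and the document commits to none of these.

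**What to change.** For each secondary outcome, state that:
- the model adjusts for the 3-month value as well as the month-0 value;
- the outcome visits are 6, 12 and 18 months or, equivalently in purpose, all visits are modelled with the arms constrained to be equal at months 0 and 3;
- the reported effect is the 12-month arm difference from arm by categorical visit.

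The mediation models count change from baseline as well, so the choice of reference visit should be settled there at the same time.

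The cost is wording only. The 3-month assessment is already scheduled for everyone before randomisation, and the change can be made before any analysis. It is a free improvement: no new data and no change to the sample size.
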